### Statistics

#### Sample size

The sample size calculation is based on two sets of data. In the LADIS observational prospective study, which included a similar population [13], there was progression in cognitive decline in 31% of the initial sample after 1 year of follow-up (200 participants out of 639 participants included). In the Osaki-Tajiri Project [72], which studied conversion to dementia in a similar population and measured different severities of cerebrovascular pathology (as in our study), odds ratios (ORs) between 2.12 and 6 were found to be implicated in the conversion into vascular dementia. We used an OR of 4 in our calculation of the expected effect (which is clinically significant).

Using Open Epi software [73] for sample calculation in randomised trials, we realised a number of 117 subjects in each arm with 95% confidence intervals (alfa of 0.05) and 80% power, giving a total of 234 subjects to be recruited. Loss to follow-up is usually 20% in this type of follow-up study, and thus a total of 280 subjects is estimated as being needed.

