### Randomisation and masking

After the 4-week run-in period, research personnel not involved in the recruitment, assessment, or intervention are responsible for managing the randomisation process using a statistical program. The randomisation sequence is generated by R software [69]. Participants are randomly assigned (1:1) to either the intervention group (IG) or to the best practice usual care group (CG), stratified by gender.

All follow-up assessments (physical, neuropsychological, and clinical diagnosis), and also the neuroradiological evaluation, are blinded to treatment allocation, as well as in the data set registry.

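### The stated planning inputs (31% decline, odds ratio of 4, 5% alpha, 80% power) do not give 117 per arm, and the article does not show which figure slipped

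*Protocol article*

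**What the plan says.** All the inputs but one are in the protocol article under Statistics, Sample size.

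- Event rate, from an observational cohort described as similar: "there was progression in cognitive decline in 31% of the initial sample after 1 year of follow-up" (200 of 639).
- Source of the effect, a second cohort graded by severity of cerebrovascular pathology: "odds ratios (ORs) between 2.12 and 6 were found to be implicated in the conversion into vascular dementia".
- Effect adopted: "We used an OR of 4 in our calculation of the expected effect (which is clinically significant".
- Result: "we realised a number of 117 subjects in each arm with 95% confidence intervals (alfa of 0.05) and 80% power", which makes 234 in total.
- Attrition: "Loss to follow-up is usually 20% in this type of follow-up study, and thus a total of 280 subjects is estimated as being needed".

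The remaining input, the 1:1 allocation, is under Randomisation and masking. The article gives no expected rate for the intervention arm, no direction for the odds ratio, and no statement of whether the test is one- or two-sided.

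**The concern.** An event rate, an odds ratio, alpha, power and an allocation ratio together fix the sample size. All five are given or readily inferred here, so the reported number can be checked, and it is about twice what the inputs require.

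What suffers is the reading of the result. A reader who takes the section at face value will think the trial has 80% power only for a fourfold change in odds. With 117 per arm it would have that power for a considerably smaller effect, so a null result would be misread.

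The basis for the effect is a second weakness. By the article's own description, the quoted odds ratios relate severity of cerebrovascular pathology to conversion to vascular dementia. That is a risk-factor association with a different outcome. It does not measure what exercise does to cognitive decline.

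**Working it through.** **Inputs.** Control risk p0 = 0.31 (the only event rate given; the article does not label it the control-arm risk). Odds ratio 4, tried as 0.25 (protective) and as 4 (upward). Alpha 0.05, taken as two-sided because the text refers to 95% confidence intervals. Power 80%. Allocation 1:1. So z(0.975) = 1.960, z(0.80) = 0.842 and (1.960 + 0.842)² = 7.849.

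**Second proportion.** p1 = odds0 × OR / (1 + odds0 × OR), with odds0 = 0.31/0.69 = 0.4493.
- OR 0.25: 0.1123/1.1123 = 0.101
- OR 4: 1.797/2.797 = 0.642

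**Formulas, n per arm,** with pbar the mean of p0 and p1, and d = p0 − p1:
- Kelsey: 2 × pbar(1 − pbar) × 7.849 / d²
- Fleiss: [1.960 × √(2 pbar(1 − pbar)) + 0.842 × √(p0(1 − p0) + p1(1 − p1))]² / d²
- Fleiss with continuity correction: (n/4) × [1 + √(1 + 4/(n|d|))]², with n from Fleiss

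**Attempt to reproduce 117 from the stated inputs.** For 31% vs 10.1%: pbar = 0.2055, pbar(1 − pbar) = 0.1633, d = 0.2090, d² = 0.04369.
- Kelsey: 2 × 0.1633 × 7.849 / 0.04369 = 58.7
- Fleiss: (1.960 × 0.5714 + 0.842 × 0.5520)² / 0.04369 = 57.5
- With continuity correction: 66.7

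| Inputs | Kelsey | Fleiss | Fleiss, corrected |
|---|---|---|---|
| 31% vs 10.1% (OR 0.25) | 58.7 | 57.5 | 66.7 |
| 31% vs 64.2% (OR 4) | 35.4 | 34.2 | 40.0 |

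Other variants do not close the gap. The unpooled formula gives 55 for the protective direction, one-sided tests give 44 to 55, and a risk ratio of 4 (31% vs 7.75%) gives 45 to 53. Using 200/639 = 31.3% in place of 31% moves the protective figures by less than 1. Power at 117 per arm for 31% vs 10.1% is 98.1% (97.1% with continuity correction).

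**What does give about 117.**

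| Reading | Kelsey | Fleiss |
|---|---|---|
| Risk halved, 31% vs 15.5% (OR 0.41) | 116.6 | 115.4 |
| OR 2.12 upward from 31% (31% vs 48.8%) | 119.0 | 117.8 |
| OR 0.25 on a 15% baseline (15% vs 4.2%) | 117.5 | 116.3 |
| OR 0.25 on 31%, both arms together | 2 × 58.7 = 117.3 | 2 × 57.5 = 115 |

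With 200/639 as the baseline, the halved-risk reading gives 115.1 (Kelsey), so even that fit is close and not exact.

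**What the planned enrolment can detect.** 280 × 0.80 = 224, or 112 evaluable per arm. At 112 per arm, power for 31% vs 15.5% is about 79%. Power reaches 80% at about 31% vs 15.3%, an odds ratio of (0.153/0.847)/(0.31/0.69) = 0.40.

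**The case against.** The best defence is that nothing harmful follows. For the effect the article names, 117 per arm is about twice what is needed, so the trial is not underpowered for its own claim, and no participant, visit or analysis has to change. That is true. It limits the consequence to interpretation, but it does not make the sample-size statement correct.

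A reader might go further and infer that the odds ratio is the error and that the trial was really sized for a halving of risk. The documents do not support that. A halved risk and 15.5% appear nowhere in the article, and three other readings fit about as well. Under one of them, a two-arm total taken as per arm, the odds ratio of 4 is the intended effect and the sample size is the slip.

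A reader might also say that the trial is sized for a 75% reduction in odds. That assumes the protective direction, which the article never states. Nor is it a defect that 117 per arm falls short of the 157 to 158 needed for a protective odds ratio of 2.12 (31% vs 17.5%), because 2.12 was quoted as the lower end of a range and was not chosen as the planning effect.

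The objection to the source of the odds ratio concerns justification, not arithmetic. It rests on the article's description, since the cited cohort is not at hand.

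**Conclusion.** The sample-size statement is wrong as written. Its inputs call for 57 to 67 per arm in the protective direction or 34 to 40 in the other, against 117 reported. The gap of about twofold is too wide for rounding, choice of formula, continuity correction or sidedness to explain.

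The conclusion assumes that 31% is the comparison-group risk and that the calculation was a simple comparison of two proportions with equal arms. It goes no further than this: the event rate, the odds ratio and the sample size are mutually inconsistent, and the text does not reveal which of them is at fault. It does not show that the trial is too small.

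**What to change.** Recover the inputs entered in the sample-size software. Then restate the control risk, the intervention risk, the direction of the odds ratio, alpha with its sidedness, and power, so that together they reproduce the stated number per arm.

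If the enrolment of 280 is kept, state the detectable effect for the 112 evaluable per arm expected after 20% loss: 80% power, two-sided 5%, for about 31% vs 15.3% (odds ratio about 0.40). Restating it as 117 evaluable per arm would introduce a new inconsistency, because 280 with 20% loss does not leave that many.

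Do not present the pathology-severity odds ratios for conversion to dementia as the source of a treatment effect; give a separate reason why an effect of the stated size is worth detecting.

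The cost is a few sentences and a restated detectable effect. No extra enrolment is required.

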**Methods:**

AFIVASC is a multi-centre randomised controlled trial, with a 6-month intervention treatment and an additional follow-up of 6 months, that aims to estimate the impact of 6 months of moderate intensity physical activity on cognition (the primary outcome) at 6 and 12 months in subjects with VCI. Participants are community dwellers with criteria for VCI without dementia or who have had previous stroke or transient ischaemic attack (TIA). Patients may be self-referred or referred from a medical appointment. After confirming the inclusion criteria, a run-in period of 1 month is conducted to access adherence; only after that are subjects randomly assigned (using a computerised program blinded to clinical details) to two groups (intervention group and best practice usual care group). The intervention consists of three physical activity sessions of 60 min each (two supervised and one unsupervised) per week. The primary outcome is measured by the presence or absence of decline in cognitive status. Secondary outcomes include changes in neuro-cognitive measures, quality of life, and functional and motor status. Primary and secondary outcomes are evaluated at 6 and 12 months by investigators blinded to both intervention and randomisation. A required sample size of 280 subjects was estimated. Statistical analyses will include regression analysis with repeated measures. The study was approved by the Ethics Committee for Health of Centro Hospitalar de Lisboa Norte (ref. no. 1063/13) and by the Ethics Committee for Health of Centro Hospitalar do Porto CHP (ref. no. 2016.055(049-DEFI/048-CES)).

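### The 20% loss allowance multiplies by 1.2 instead of dividing by 0.8, so 280 subjects leave 224, not the 234 the plan names (minor)

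*Protocol article*

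**What the plan says.** The Sample size section of the protocol article gives the design settings as "with 95% confidence intervals (alfa of 0.05) and 80% power". It reports the result as "we realised a number of 117 subjects in each arm", "giving a total of 234 subjects to be recruited". The allowance for attrition follows directly: "Loss to follow-up is usually 20% in this type of follow-up study, and thus a total of 280 subjects is estimated as being needed".

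The Abstract (Methods) repeats the final figure: "A required sample size of 280 subjects was estimated". Allocation is equal between the arms (Randomisation and masking). The article gives no other loss rate and no other route to 280.

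**The concern.** The wording presents 280 as the consequence of two numbers, 234 and 20%. For that to hold, 80% of 280 would have to be at least 234, and it is not. The allowance appears to add 20% of the target number of completers, whereas a 20% loss to follow-up removes 20% of those enrolled.

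At stake is whether the stated total, the stated attrition and the stated number behind the power can all be true together. Someone who later compares observed attrition with the plan would take a 20% loss as provided for, when the total provides for rather less.

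**Working it through.** **Inputs**, all from the Sample size section except the allocation ratio (Randomisation and masking):

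- required before loss: 117 per arm, 234 in total
- loss to follow-up: d = 20%
- stated total after the allowance: 280
- allocation 1:1

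**Reproducing the plan's figure.** n × (1 + d) = 234 × 1.2 = 280.8, which becomes 280 when rounded down. This matches the stated total.

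**What 280 leaves at 20% loss.** 280 × (1 − 0.20) = 224, or 112 per arm. The shortfall is 234 − 224 = 10 in total, 5 per arm.

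**The loss that 280 does cover.** 1 − 234/280 = 46/280 = 16.4%.

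**The total that keeps 234.** n / (1 − d) = 234 / 0.8 = 292.5, so 293. For equal arms, 117 / 0.8 = 146.25, so 147 per arm and 294 in total. That is 13 to 14 more than 280. Rounding does not explain the gap: it accounts only for the step from 280.8 to 280, which also goes downward.

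**Size in terms of power.** This step needs an assumption: that 117 per arm gives exactly 80% power in a two-sided test at 0.05. The standardised effect then grows with the square root of the sample size:

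- at 117 per arm: 1.960 + 0.842 = 2.802
- at 112 per arm: 2.802 × √(112/117) = 2.802 × 0.978 = 2.741
- power = Φ(2.741 − 1.960) = Φ(0.781) ≈ 78%

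**Why that is only an assumption.** The section names a 31% rate and an odds ratio of 4. The odds at 31% are 0.31/0.69 = 0.449.

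| Direction of OR 4 | Second proportion | n per arm for 80% power | Power at 112 per arm |
|---|---|---|---|
| Decline reduced (OR 1/4) | 10.1% | 58 | 97.6% |
| Decline raised (OR 4) | 64.2% | 35 | above 99.9% |

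These use a two-sided normal-approximation test without continuity correction; with the correction the sizes are 67 and 41. Neither direction gives 117. The article therefore does not fix the effect to which 117 belongs, and the 78% cannot be tied to an effect that the plan states.

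**The case against.** **The lost subjects are not wholly lost.** The Data analysis section plans an intention-to-treat analysis with a GEE logistic model on the 6- and 12-month outcomes, so a person lost after month 6 still contributes. The attendance section keeps following those who stop the sessions, where they allow it. This stands as partial mitigation: 224 is the number left if everyone lost counts as lost, which is how the plan's own allowance treats them. It does not repair the arithmetic, because 12 months is named as the primary marker of success and the 31% reference rate is a one-year figure.

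**The 20% is only a rounded expectation.** True: the section describes it as the usual figure, and a loss of 16.4% or less would be covered. That argues for a low grading. It does not make 280 follow from 234 and 20%.

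**The trial is underpowered.** A reader might infer this, and the document does not support it. On the stated 31% and odds ratio of 4, 112 per arm has power of about 98% or more. Power falls below 80% only if 117 per arm is accepted as the true requirement. It is also tempting to quote power for a back-solved effect, such as 31% against 15.5%, which roughly reproduces 117. The article states no such effect, it conflicts with the odds ratio of 4, and it is not the only candidate: 31% with an odds ratio of 2.12, the lower end of the cited range, gives 118 per arm.

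**The counting point is unclear.** The article speaks of subjects recruited and needed, while randomisation follows a 4-week run-in. Reading 280 as the number randomised is an interpretation. If 280 is counted at inclusion, losses during the run-in would widen the gap.

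**Conclusion.** The stated total is wrong as derived. At the plan's own 20% loss, 280 subjects leave 224 (112 per arm), 10 short of 234, and 280 covers a loss of 16.4%. This part rests only on printed figures and on counting each lost subject as lost.

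The consequence is minor: about 78% power instead of 80%, on the assumption that 117 per arm gives exactly 80%. The finding is that 280 does not leave the number the plan says it needs. It is not a finding that the trial lacks power for its stated effect. That 117 does not follow from 31% and an odds ratio of 4 is a separate matter, and this correction does not settle it.

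**What to change.** Compute the allowance as n / (1 − d) and restate the last sentence of the Sample size section in one of these ways:

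1. 280 subjects allow for a loss to follow-up of about 16%, leaving 234 evaluable.
2. 280 subjects with 20% loss leave 224 evaluable (112 per arm), with slightly less than the stated 80% power.
3. If 234 evaluable are to be kept at 20% loss, the total is 293, or 294 (147 per arm) for equal arms.

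Keep the Abstract consistent with the choice. Do not add a 31% against 15.5% effect to the text, since the plan does not state one.

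The first two options cost one sentence and no extra subjects; the price is a lower tolerated loss or a slightly less favourable power statement. The third costs 13 to 14 more subjects.

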#### Data analysis

Data will be registered according to the Consolidated Standards of Reporting Trials (CONSORT) guidelines for randomised controlled trials [19]. We will use intention-to-treat analyses as the primary analysis with all participants included according to initial group allocation. For the primary outcome analysis (dependent variable: cognitive decline according to clinical criteria), we will conduct a logistic regression analysis. Since the outcomes are measured at 6 and 12 months, we will fit a generalised estimating equations (GEE) logistic regression model for the data. The models will adjust for covariates which are assumed to interfere with cognition in the follow-up (age, gender, education, and baseline MoCA). For secondary outcomes, logistic or linear regression analysis will be used as applicable.

For each of the outcome endpoints (i.e. transition of cognitive status and change in neuropsychological evaluation through composite or global scores) the change from baseline to 6 months and 12 months will be assessed, even though we will consider 12 months as the primary marker of success.

Observing a statistically significant difference on any of the outcomes will be considered preliminary evidence of efficacy. We will also report variances, co-variances, and effect sizes, as well as sampling feasibility (i.e. ease of recruitment, recruitment rate, withdrawal rate).

The same qualified statistician involved in the statistical analysis designed the SAP and will independently review the analysis according to the plan.

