## Methods/design

### Design

AFIVASC (“physical activity in vascular cognitive impairment’) is a Portuguese multi-centre, randomised parallel group trial comparing a 6-month intervention of two moderate physical activity sessions and one unsupervised moderate physical activity session per week with an additional follow-up of 6 months to evaluate its long-term impact in comparison with the current best practice usual care. The Consolidated Standards of Reporting Trials (CONSORT) statement [19] has been used as a framework for the development of our methodology (Fig. 1). To ensure adherence, a run-in period will be conducted after inclusion. This run-in period consists of a 4-week period before randomisation during which all participants are assigned to equal procedures, namely the educational session and all planned assessments. After the run-in period, participants are randomised into two parallel groups (best practice usual care group and the intervention group). The best practice usual care group will receive the standard usual care, but they are allowed to perform physical activity by self-initiative, although supervised physical intervention is not allowed. The control of the amount of physical activity per week is performed in both groups through accelerometry. We do not expect to see high levels of physical activity in the usual care group since VCI is usually associated with a reduced initiative.

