### Participants

#### Recruitment and study setting

The study is conducted in the University of Lisbon at the Faculdade de Medicina and Instituto de Medicina Molecular in Lisbon, and the Hospital de Santo António, Centro Hospitalar do Porto. The Human Kinetics Faculty (from the University of Lisbon) is a partner of the study. These centres, both urban and academic, have experience in the diagnosis and management of patients with cognitive decline of a vascular aetiology and in stroke care. Subjects are referred to each participating centre directly from the community (participants can be self-presenting, as the study was advertised in public spaces) or from a medical appointment (general family doctor in primary care, or from neurological, mental health, memory clinics, or hospital settings). Participants can be referred to the study due to minor cognitive complaints/symptoms or minor behavioural changes attributed to a cerebrovascular aetiology. Patients can also be referred if they had a previous stroke or transient ischemic attack (TIA), even without complaints, if neuropsychological evaluation showed evidence of any change considered to be due to a cerebrovascular aetiology. Post-stroke cognitive impairment is common even after successful clinical recovery from a stroke episode, and a recent study showed that at least one cognitive domain was impaired in 83% of cases [20]. Considering TIA, more than one cognitive domain was impaired in more than a third of patients 3 months after a TIA [21].

Eligible subjects are contacted by the recruitment team to further explain the procedures of the study and to confirm inclusion and exclusion criteria. Written informed consent is given by participants and informants. This consent allows access to the subject’s clinical records for research purposes and indicates their willingness to participate in all the activities inherent to the study. Those remaining eligible and without contraindications to physical activity are contacted by an investigator and proceed to baseline assessments.

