### Study outcomes

The primary outcome measure will be cognitive decline defined as a dichotomous variable (decline/no decline) through cognitive status criteria as described in the Assessments section below. The secondary outcomes are changes in neurocognitive scores of at least 1.5 standard deviation (SD) from baseline to endpoint (using *z* scores), a decline in the raw values of neuropsychological tests, in quality of life, functional and motor status, and falls.

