**Fig. 2 Fig2:**
[figure not shown]
Study schedule

In all assessments (baseline and follow-up clinical visits), the cognitive status of patients is classified into the following groups: 1) diagnosis of dementia; and 2) diagnosis of cognitive impairment with no dementia according to clinical, neuropsychological, and functional criteria. For this purpose, we used the usual criteria and definitions of the Diagnostic and Statistical Manual of Mental Disorders (edition 4 revised; DSM-4TR) [25]. At baseline, patients could only fulfil VCI without dementia defined as evidence of cognitive impairment and clinical consensus to identify significantly related vascular features; exclusion of dementia when impairments were not sufficiently severe to interfere with social or occupational functioning or when impairments were more focal than the global requirement for a diagnosis of dementia. For follow-up we considered the following criteria for subtypes of dementia: probable Alzheimer disease [26]; probable vascular dementia [27]; subtype of subcortical vascular dementia [28]; frontotemporal dementia [29]; and Lewy body dementia [30]. The criteria for Alzheimer’s disease with a vascular component was made when the investigator judged that the clinical picture presented both aspects of Alzheimer’s disease and vascular dementia.

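### Centre is missing from both the stratification and the listed covariates of this two-centre trial, and the continuous secondary change scores have no stated own-baseline term: a minor, cheaply mended loss

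*Protocol article*

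**What the plan says.** The Design section of the protocol article says the study "is a Portuguese multi-centre, randomised parallel group trial". Recruitment and study setting names one site in Lisbon and one in Porto, and adds: "These centres, both urban and academic, have experience in the diagnosis and management of patients with cognitive decline of a vascular aetiology". The number of participants expected from each is not given.

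Randomisation and masking names a single stratification factor: "Participants are randomly assigned (1:1) to either the intervention group (IG) or to the best practice usual care group (CG), stratified by gender".

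The primary outcome is binary (Study outcomes): "The primary outcome measure will be cognitive decline defined as a dichotomous variable (decline/no decline". For its analysis at 6 and 12 months, the Data analysis section says "we will fit a generalised estimating equations (GEE) logistic regression model for the data". The next sentence gives the adjustment set: "The models will adjust for covariates which are assumed to interfere with cognition in the follow-up (age, gender, education, and baseline MoCA". The list ends there.

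The sentence after that covers the rest: "For secondary outcomes, logistic or linear regression analysis will be used as applicable". It has no covariate list of its own. The same section says that change from baseline to 6 and to 12 months will be assessed. Study outcomes describes the secondary outcomes as changes or declines in neuropsychological scores, quality of life, functional and motor status, together with falls.

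On entry status, the Assessments section says: "At baseline, patients could only fulfil VCI without dementia".

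**The concern.** Gender is both stratified on and adjusted for. Centre gets neither, although the article gives reasons why it could predict the outcome. Participants reach the trial by several routes (self-referral after advertising, primary care, memory clinics, hospital), so case-mix may differ by site. The primary outcome is a clinical classification, and the article describes no central adjudication for it, whereas it does describe central reading for MRI. The intervention relies on supervised sessions over six months. By the plan's own test, that a covariate should be one expected to influence cognition during follow-up, centre is a natural candidate.

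Two things are at stake. First, the arms can differ by chance in their mix of centres, with no stated means of accounting for it. Second, for continuous secondary outcomes analysed as change, the only baseline score listed is MoCA. The neuropsychological, quality-of-life and motor measures are all taken at baseline. Leaving out an outcome's own baseline loses some precision and lets a chance baseline difference carry into the change score through regression to the mean.

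**Working it through.** The article gives no figure on this point to reproduce. Its sample-size calculation contains no centre or covariate term and does not depend on the issue.

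**Inputs from the article:** N = 280, allocated 1:1, so 140 per arm; 234 before allowance for loss; a decline rate of 31% at one year (Sample size).

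**Assumed, because the article does not give them:** the share s of participants from one centre (0.5 or 0.8); the gap d in decline rate between centres (5, 10 or 20 points); the baseline to follow-up correlation rho (0.5, 0.7 or 0.8).

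**Step 1. Chance imbalance in centre share, allocation not stratified by centre.**

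SD of the between-arm difference = √[s(1−s)/140 + s(1−s)/140] = √[4s(1−s)/280].

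- s = 0.5: √(1/280) = 0.0598; 1.96 × 0.0598 = 0.117, or ±11.7 points. Chance of a difference above 10 points: 9.4%.
- s = 0.8: √(0.64/280) = 0.0478; 1.96 × 0.0478 = 0.094, or ±9.4 points. Chance of a difference above 10 points: 3.6%.

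**Step 2. Effect on the unadjusted risk difference.** Shift at a 1.96-SD imbalance = 1.96 × SD × d.

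**Step 3. Share of outcome variance due to centre (linear risk scale).** s(1−s)d² / (0.31 × 0.69), where 0.31 × 0.69 = 0.2139. Multiplying by 234 gives a rough equivalent in participants.

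| Assumed gap d | Shift, 50:50 | Shift, 80:20 | Variance share, 50:50 | Variance share, 80:20 | Equivalent of 234, 50:50 / 80:20 |
|---|---|---|---|---|---|
| 5 points | 0.59 points | 0.47 points | 0.29% | 0.19% | 0.7 / 0.4 |
| 10 points | 1.17 points | 0.94 points | 1.17% | 0.75% | 2.7 / 1.8 |
| 20 points | 2.34 points | 1.87 points | 4.68% | 2.99% | 10.9 / 7.0 |

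The 20-point row at a 50:50 split combines the largest assumed gap with the split that allows most imbalance. The shift is the value at 1.96 SD, not a maximum.

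**Step 4. Own baseline for a continuous outcome** (equal variances at baseline and follow-up, no other covariates).

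Variance factor for the change score: 2(1−rho). Variance factor with the baseline as covariate (ANCOVA): 1−rho². Ratio: (1−rho²) / [2(1−rho)] = (1+rho)/2.

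- rho = 0.5: 0.75 / 1.00 = 0.75
- rho = 0.7: 0.51 / 0.60 = 0.85
- rho = 0.8: 0.36 / 0.40 = 0.90

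The saving is therefore at most 10-25% of variance over this range. It is smaller where age, gender, education and MoCA, if they are in the model, already explain part of the baseline value.

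**The case against.** **A reader might infer that the primary comparison is biased.** It is not. Randomisation protects the comparison on average, and chance imbalance is already reflected in its standard error. With a gap of 5-10 points between centres, the shift is only about 0.5-1.2 points and centre is worth about 3 participants or fewer out of 234. This stands, and it is why the point is minor.

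**A reader might infer that every outcome lacks its own baseline.** The article does not support that. All participants enter with the same cognitive status, so the primary outcome has no baseline variation to adjust for, and baseline MoCA is already listed.

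**A reader might infer that the secondary models are fixed with MoCA as their only baseline score.** The covariate sentence directly follows the primary GEE model, and the secondary sentence has no list. The abstract also mentions regression with repeated measures, which can take in the baseline, and an SAP exists that is not shown. The own-baseline part is therefore the weaker one: a recommendation to state the term, not a demonstrated error. The centre part is different, because the article itself enumerates both the stratification factor and the primary covariates.

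**A reader might infer that the two sites use different assessors and diagnostic thresholds.** The article does not say how assessors or exercise physiologists are divided between sites, and the diagnostic criteria and test battery are common to all. A centre difference is plausible but not shown.

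**A reader might expect a precision gain in the primary model.** In logistic regression, adjustment does not shrink the standard error of the log odds ratio. Any benefit is in power, and here it would be small. The article also states no planned risk difference against which to set the shifts.

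**Conclusion.** Centre is absent from both the stated stratification and the enumerated covariates of a two-centre trial. The consequence is unmanaged chance imbalance and a small loss of efficiency: about 0.5 to 2.3 points on the risk difference at a 1.96-SD imbalance, across assumed centre gaps of 5 to 20 points and assumed splits of 50:50 to 80:20. These figures treat allocation as unrestricted with respect to centre. If each centre in fact has its own allocation list, which the article does not say, the imbalance would be smaller, but centre would then belong in the model as a design factor.

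For continuous secondary outcomes analysed as change, other than MoCA, including the own baseline would cut variance by at most 10-25% for assumed correlations of 0.8 down to 0.5. It has no bearing on the sample size, which rests on the binary primary outcome. Overall severity is minor.

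**What to change.** 1. Add centre as a fixed effect to the primary GEE logistic model and to the secondary models. This is one extra term, already known for every participant, and a few words in the analysis plan before unblinding.
2. For each continuous secondary outcome analysed as change, add that outcome's own baseline value as a covariate. The values are already collected, so the cost is again only wording. MoCA needs no second term, and the primary outcome none.
3. Optionally, if recruitment is still open, stratify the remaining randomisation by centre and gender (2 × 2 = 4 strata). This costs more than wording: under Study supervision and ethics, a protocol modification goes to the Ethical Committee after Steering Committee discussion, and the allocation list must be regenerated. It cannot help participants already randomised, so item 1 is needed in any case.
4. Report the number of participants by centre and arm, so that readers can see what imbalance occurred.
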